### Variables

A SPIRIT schedule of enrollment, interventions, and assessments is reported in **Fig 1**.

**Fig 1 pone.0300945.g001:**
[figure not shown]
SPIRIT schedule of enrolment, interventions, and assessments.

### Baseline data

➢ Age, sex, educational level, occupation (current or previous), body mass index (BMI, Kg/M^2^), absence of smoking habit or active smoking expressed as pack/years (= number of cigarettes per day multiplied by the number of years the person has smoked/20), years of COPD, GOLD classes (1, 2, 3, 4) and GOLD grades based on GOLD 2011 (A, B, C, D) and GOLD 2023 reports (A, B, E) (www.goldcopd.org), frailty score using the Clinical Frailty Scale (**Fig 2**), list and number of comorbidities, list and number of drugs taken.

**Fig 2 pone.0300945.g002:**
[figure not shown]
Clinical frailty scale.

### Cardiovascular events

These will be defined as the following. Any ICD-10 code reported in **Table 1** or the following event recorded in the hospital notes at 1 and 2 years will be considered as a cardiovascular event.

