## Introduction

Frailty is a clinical syndrome that increases vulnerability to stressors due to decline of multiple physiological reserves. People living with frailty area at higher risk of falls, disability, long hospitalisations, access to care homes, and death [1]. There are two principal approaches of identification of frailty: the deficit accumulation model and the phenotype model [1, 2]. Based on these models, different tools have been created and validated to assess frailty in clinical practice [3].

Chronic diseases such as Chronic Obstructive Pulmonary Disease (COPD) increase the risk of frailty [3, 4]. Literature on frailty in COPD have been emerging in the recent years. While frailty is not synonym for ageing, it is well known that people over 65 years are more likely to live with frailty [4]. In addition, prevalence of COPD increases with age [5]. A double probability of being frail has been demonstrated in patients with COPD compared to patients without COPD in the paper of Marengoni et al. The study reported a prevalence of frailty in COPD between 9% and 64% based on the phenotype model and from 9% to 28% using different frailty assessment instruments [6]. Studies have shown that frailty can increase the risk of mortality in patients with confirmed diagnosis of COPD according to GOLD guidelines (www.goldcopd.org) [7–12].

Cardiovascular diseases share common risk factors with COPD such as ageing, active smoking, and sedentary lifestyle. COPD and CVD frequently co-exist and are associated with worse outcomes than either condition alone. Additionally, the risk of cardiovascular events is higher after COPD exacerbation [13, 14]. Cardiovascular comorbidities are very common in patients with COPD and can increase the risk of death in this population [5, 15, 16].

The present protocol describes a research study project on patients with COPD to investigate the influence that frailty can have on the risk of cardiovascular events in these patients. The project will assess the association between frailty and cardiovascular mortality, and the relationship between frailty and all-cause mortality and COPD-related mortality. Our team have widely collected data on frailty previously using routinely collected service evaluation level data.

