**Coronary artery disease (CAD)**	
Angina	**I20**
Acute Myocardial Infarction (AMI)	**I21**
Heart failure	**I50**

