**Aortic disease**	
Aortic aneurysm	**I71.2**
Abdominal aneurysm	**I71.4**
**Peripheral artery disease (PAD)**	**I73**

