**Arrhythmias**	
Atrial fibrillation and flutter	**I48**
Other cardiac arrhythmias	**I49**

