### Primary outcome

➢ Number of cardiovascular events (including hospital admissions due to cardiovascular cause) at 12 and 24 months in COPD patients living with frailty *vs* non-frail COPD patients.

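### The event definition counts any listed code found in the hospital notes, so a long-term condition noted at a non-cardiovascular contact can enter the primary count

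*Protocol article*

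**What the plan says.** The operative definition of an event is in the protocol article under *Cardiovascular events*: "Any ICD-10 code reported in Table 1 or the following event recorded in the hospital notes at 1 and 2 years will be considered" one. It names a code list and a source. It does not mention diagnosis position, reason for contact, new or acute onset, or how repeated recordings are handled.

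Table 1 mixes acute events with conditions that can persist for years, among them "Heart failure" (I50), "Atrial fibrillation and flutter" (I48), angina (I20) and peripheral artery disease (I73).

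The *Primary outcome* section, like *Aims*, makes the outcome a count: "Number of cardiovascular events (including hospital admissions due to cardiovascular cause) at 12 and 24 months". *Statistical analysis* models that count by zero-inflated Poisson regression across three frailty groups. It adjusts for sex, age, frailty at recruitment and non-respiratory comorbidities.

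Two statements in the *Introduction* bear on the point: "Cardiovascular comorbidities are very common in patients with COPD", and "People living with frailty area at higher risk of falls, disability, long hospitalisations, access to care homes, and death". The exclusion criteria do not remove patients with existing cardiovascular disease.

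**The concern.** Taken literally, the definition accepts a listed code whatever brought the patient to hospital. A patient with known atrial fibrillation who attends for a COPD exacerbation may have I48 in the notes of that contact, and the wording lets it count although nothing cardiovascular happened. A condition first diagnosed after entry can likewise be recorded again at later, unrelated contacts.

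Part of the primary count can therefore reflect how often a patient is seen in hospital for other reasons. If that frequency rises with frailty, the outcome is misclassified differentially by exposure, and in the direction of the study hypothesis. The primary result could then show an association between frailty and cardiovascular events that is partly an association between frailty and hospital use.

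Adjusting for comorbidities deals with who carries a listed condition. It does not deal with how often that condition is written down after entry.

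**Working it through.** **Plan's own figure.** The only calculable figure is the sample size, which this point does not dispute. For 40% against 60%, two-sided alpha 0.025 and 80% power: n = [2.2414 × √(2 × 0.5 × 0.5) + 0.8416 × √(0.24 + 0.24)]² / 0.20² = (1.5849 + 0.5831)² / 0.04 = 117.5, so 118 per group. The plan has 120, with power 80.9%.

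**Passages side by side.** *Cardiovascular events* admits any listed code in the notes. *Primary outcome* and *Aims* mention admissions with a cardiovascular cause, but only in the phrase "including hospital admissions due to cardiovascular cause". A phrase that starts with an inclusion adds to or illustrates the count; it does not limit it. The narrower intent it suggests therefore does not restrict the definition.

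**Illustration.** The documents give no rate of admission or of code carriage. All inputs here are assumptions:

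- no true frailty effect;
- 0.5 true cardiovascular events per patient-year in every group. With Poisson counts this gives 1 − e^(−0.5) = 39% with any event, close to the 40% that *Power and sample size* assumes for the non-frail;
- 40% of each group carry a long-term Table 1 condition;
- 80% of carriers' non-cardiovascular admissions record it, and each recording counts.

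Expected count = 0.5 + admissions × 0.4 × 0.8.

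| Admissions per year (CFS 1–3 / 4–5 / 6–8) | Expected counts | Ratio 4–5 | Ratio 6–8 |
|---|---|---|---|
| 0.2 / 0.4 / 0.6 | 0.564 / 0.628 / 0.692 | 1.11 | 1.23 |
| 0.3 / 0.6 / 1.0 | 0.596 / 0.692 / 0.820 | 1.16 | 1.38 |
| equal in all groups | equal | 1.00 | 1.00 |

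**False positives.** Studies of 120:120:80 were simulated and analysed by Poisson regression with robust standard errors at two-sided 0.025. This is simpler than the planned zero-inflated model. Without covariates, the first row gave 5–6% (CFS 4–5) and 12–13% (CFS 6–8), and the second row 9–10% and 30–34%. Equal admissions gave about the nominal 2.5%.

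**Effect of adjustment.** With carrier status in the model, the first row gave 6% and 14%, and the second about 10% and 36–37%. Adjustment does not help here, because carriage is equal and only the number of admissions differs.

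**If a carried code counts once per patient.** Expected count = 0.5 + 0.4 × (1 − e^(−0.8 × admissions)). The first row becomes 0.559 / 0.610 / 0.652, with ratios 1.09 and 1.17. The second becomes 0.585 / 0.652 / 0.720, with ratios 1.11 and 1.23. The bias shrinks but remains.

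**The case against.** The strongest reply is that the protocol says which conditions qualify and does not say that every later recording is a new event. That is correct. A reader might infer that three exacerbation admissions in a patient with atrial fibrillation must score three events. The text does not say so; it only fails to prevent it. The supported statement is that such recordings can score.

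A reader might also infer a flat contradiction between *Cardiovascular events* and *Primary outcome*. The two are in tension, since one suggests a narrower intent than the other states, but both can be true as written. They need reconciling.

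Third, the *Introduction* links frailty to falls and to long hospital stays. Length of stay is not number of admissions, and the mechanism needs number. That frail patients have more non-cardiovascular contacts is plausible, but it remains an assumption. So does the frequency with which these conditions are carried as secondary codes.

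Fourth, much larger figures can be produced. With 0.2 true events, 0.3/0.6/1.0 admissions and carriers of 30/40/50%, the expected counts are 0.272 / 0.392 / 0.600 and the ratios 1.44 and 2.21, with false positives near 25% and 85%. These should not be relied on. Part is ordinary comorbidity confounding, which the plan addresses: adjusting for carriage lowers the ratios to about 1.27 and 1.75 and the false positives to about 12% and 60%. A mean of 0.272 also implies at most about 1 − e^(−0.272) = 24% of CFS 1–3 patients with any event, against the plan's 40%.

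Finally, the CRF is in a supplement that is not shown and may already record diagnosis position. That affects the cost of the fix. It does not narrow a definition that the article states outright.

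**Conclusion.** The point holds as a definition fixed too broadly, and it is not a detail merely left to a later document. As worded, long-term Table 1 conditions recorded at non-cardiovascular contacts can enter the primary count, possibly repeatedly.

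The direction of the bias depends on one assumption: that non-cardiovascular contacts become more frequent with frailty. Given that and no true effect, the rate ratio is pushed above 1 and the planned adjustment does not remove the excess. On the inputs above, the spurious ratio is 1.11–1.16 for CFS 4–5 and 1.23–1.38 for CFS 6–8, with false positives of about 5–10% and 12–35% against a nominal 2.5%. The actual size cannot be derived from the documents.

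If there is a true effect, the observed ratio is a weighted mean of the true ratio and the ratio of incidental recordings, so it no longer estimates the cardiovascular effect alone.

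**What to change.** In *Cardiovascular events*, state that a contact counts as an event only if a Table 1 condition is its principal diagnosis or the reason for the contact, or if the notes document onset or acute worsening of that condition during the contact. Align *Aims* and *Primary outcome* with that sentence. Record diagnosis position in the CRF if it is not already there, and report the any-position count as a sensitivity analysis.

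The cost is one sentence and at most one data field. The downside is small: true events coded only in a secondary position, without a note of onset or worsening, drop out of the primary count. The sensitivity analysis would show how far the result depends on excluding secondary-position codes.

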### Follow up data (12 and 24 months)

➢ Number of cardiovascular events.➢ Number of deaths due to cardiovascular cause.➢ Number of all-cause deaths.➢ Number of deaths due to COPD.➢ Frailty score using the Clinical Frailty Scale (**Fig 2**).➢ Follow up spirometry.

### Frailty assessment

We will use the Clinical Frailty Score. This has been validated for use to assess frailty in older patients [17]. The score ranks from 1 to 9 with a score of ≥4 being classed as mildly frail, and 4–5 and moderately frailty, and 6 to 9 severely frail to terminally ill. Patients scored CFS 9 (terminally ill) will be excluded. We will use the Montreal Cognitive Assessment (MoCA) test to explore cognitive function [18]. The MoCA is a tool used to assess deficits in different cognitive domains: visuospatial ability, executive function, language, memory, attention, naming, orientation, delayed recall, and abstraction. It is scored out of a total of 30 points and a cut-off of ≤26 may indicate mild cognitive impairment.

### Safety considerations

Safety reporting/adverse events will be reported by Principal Investigators. However, as this study routinely collected clinical data, there are minimal safety issues expected.

### Primary outcome

➢ Number of cardiovascular events (including hospital admissions due to cardiovascular cause) at 12 and 24 months in COPD patients living with frailty *vs* non-frail COPD patients.

### Secondary outcomes

➢ Long-term cardiovascular mortality at 12 and 24 months in COPD patients living with frailty *vs* non-frail COPD patients.➢ All-cause long-term mortality at 12 and 24 months in COPD patients living with frailty *vs* non-frail COPD patients.➢ Mortality due to COPD at 12 and 24 months in COPD patients living with frailty *vs* non-frail COPD patients.➢ Prevalence of frailty in COPD.

### Data management plan, data protection and patient confidentiality

All investigators and trial site staff will comply with the requirements of the Good Clinical Practice (GCP) and Guidelines for Data Processing in the European Union (General Data Protection Regulation-GDPR 679/2016) with regards to the collection, storage, processing and disclosure of personal information.

Where personal information is collected, it will be kept secure, and maintained. This will involve:

The creation of coded, depersonalised data where the participant’s identifying information is replaced by an unrelated sequence of characters.No patient identifiable information will be uploaded or stored on the secure database. Collaborators will anonymise patients by recording patient clinical numbers alongside database numbers in a separate secure spreadsheet to aid the collection of data locally.Limiting access to the minimum number of individuals necessary for quality control, audit, and analysis.Confidentiality of data will be preserved when the data are transmitted to co-investigators as patients will be assigned a study ID number.Data collected from sites will be via the electronic database, using freely available software such as Microsoft XL. The research team are experienced in data management. This database with be held within University of Modena (Italy) and stored for a minimum of 7 years.Data custodian and Chief Investigator is [name].

### Statistical analysis

We will aim to recruit a minimum of 320 patients: across a minimum of 3 sites.

This protocol and analysis plan will be drafted by a medical statistician fully blinded to the outcome data.

Data will be analysed for correlation between frailty and clinical outcomes. The primary analysis will be the number of cardiovascular events (time to event) at 12 and 24 months, adjusting for sex, age (18–64, 65–80, >80) and frailty at the time of recruitment, and other clinically relevant non-respiratory comorbidities. The number of events will be analysed using a zero-inflated Poisson regression to compare the rates between the three frailty groups. The rate with 95%CI will be presented alongside the p-value. Overdispersal will be assessed and if found to be present robust standard errors will be fitted.

The secondary analyses will assess the time to all-cause mortality, cardiovascular mortality, and mortality due to COPD that will be fitted to compare those classified as frail *vs* not frail visually using a Kaplan Meier plot. Data will be analysed using a multivariable Cox baseline proportional hazards regression, adjusting for covariates. The time to mortality will be calculated from the date of study entry to the end of follow up. The analyses will be presented as Odds Ratio (adjusted OR) with associated 95% confidence intervals and p-values. Subgroups analyses (age, sex, GOLD classes and grades, comorbidities) will be conducted to assess the grade of frailty. Stata version 18 (or later) will be used.

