**Methods:**

This protocol describes a European prospective cohort study of community-based people, in a stable condition with diagnosis of COPD (as defined by GOLD guidelines) across hospitals in Italy and UK. Frailty prevalence will be assessed using the Clinical Frailty Scale. At 1- and 2-year follow up, primary outcome will be the impact of frailty on the number of cardiovascular events; secondary outcomes: the influence of frailty on cardiovascular mortality, all-cause mortality, and deaths due to COPD. For the primary outcome a zero-inflated Poisson regression will compare the number of cardiovascular events at 1 year. Secondary outcomes will be analysed using the time to mortality.

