### Power and sample size

Assuming the proportion of those that are not frail (40%), mildly frail (60%) and moderately to severely frail (75%) will exhibit at least one cardiovascular event at 1 year. In order to detect these two comparisons (not frail, versus mildly frail & not frail versus moderately frail), using a chi-squared test with type-1 error = 0.025 and 80% power. We will need a minimum of 320 patients, approximately 120:120:80 for CFS 1–3, 4–5, 6–8 respectively.

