## Discussion

This protocol describes a study designed to investigate the influence of frailty on the risk of cardiovascular morbidity and mortality in patients with COPD. The study will also assess whether the frailty status can have an impact on all-cause mortality and death due to COPD.

This study will offer key real world data components to describe the complexity of COPD that is frequently associated with cardiovascular disease or other concomitant chronic diseases sharing common risk factors and playing a role in COPD prognosis. Additionally, patients with COPD have high risk of frailty that can increase their risk of mortality [7–12].

Relevant data collected includes comorbidities and GOLD grades based on the GOLD recommendations 2011 and 2023 (www.goldcopd.org) to characterise patient’s severity related to risk of exacerbation, hospitalisation, and death. The primary research questions this study will answer are whether the frailty status may be associated with the number of cardiovascular events and long-term cardiovascular mortality in a large, complete population with COPD. Answers to the questions of this longitudinal cohort study will inform chest physicians of the role of frailty in patients with COPD. More broadly, the clinical data collected in outpatient setting, including frailty, can have significant value to predict patient’s prognosis. This is a current topic in the field of respiratory research.

One limitation of the study design is the lack of a control group of individuals matched on age, sex, smoking habit, and frailty status, but without COPD. This would be useful to distinguish the potential role of COPD in the risk of development of cardiovascular disease [19].

All data will be reported as a whole cohort. Unit-level data for comparison will be fed back to collaborators to support local service improvement. This project will be submitted for presentation at a national or international Respiratory and Geriatric conference. Manuscript(s) will be prepared following close of the project. Manuscript(s) will also be prepared following interim data analysis at 12 months if numbers of patients recruited to the study at that time reach the planned sample size.

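### The primary time point is contradictory (1 year versus 12 and 24 months), and the only stated significance level, 0.025, covers two frailty contrasts at 1 year

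*Protocol article*

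**What the plan says.** **Time point.** Under Methods in the abstract, the model sentence reads "For the primary outcome a zero-inflated Poisson regression will compare the number of cardiovascular events at 1 year". Power and sample size likewise assumes proportions with at least one event at 1 year. The abstract's own outcome sentence, however, places the primary outcome at 1- and 2-year follow-up. The Aims and the Primary outcome section ("including hospital admissions due to cardiovascular cause) at 12 and 24 months in COPD patients living with frailty") name both times, as does the Statistical analysis section: "The primary analysis will be the number of cardiovascular events (time to event) at 12 and 24 months".

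**Level.** The only significance level in the document is in Power and sample size: "using a chi-squared test with type-1 error = 0.025 and 80% power". It is tied to two contrasts at that one time: "In order to detect these two comparisons (not frail, versus mildly frail & not frail versus moderately frail".

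**Endpoint and groups.** The Statistical analysis section attaches a time-to-event label to the count, then specifies a zero-inflated Poisson regression across three frailty groups. Power and sample size uses three bands: CFS 1–3, 4–5 and 6–8. The Aims and Primary outcome sections word the comparison as frail versus non-frail. Frailty assessment describes the scale as "a score of ≥4 being classed as mildly frail, and 4–5 and moderately frailty, and 6 to 9 severely frail to terminally ill", which puts 4–5 under two labels and does not match the labels in the sample size section.

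**The concern.** A reader cannot tell from the protocol whether the 12-month comparison is the primary result or one of two. The study was sized, and its error level set, for 1 year. If 24 months is equally primary, a second set of comparisons enters the primary family with no error set aside for it, and the conclusion could rest on whichever time point shows a difference. The count versus time-to-event label and the two-group versus three-group wording add to the ambiguity in the same definition. The choice should be fixed before any outcome data are analysed, because the 12-month data will exist before the 24-month data.

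**Working it through.** **1. Reproduce the sample size.** Inputs from Power and sample size: proportions 40%, 60% and 75%; type-1 error 0.025; power 80%; groups 120:120:80. Two-sidedness is assumed because it is not stated. With pooled variance and no continuity correction,

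n per group = [z(1−α/2)·√(2p̄(1−p̄)) + z(0.80)·√(p1(1−p1) + p2(1−p2))]² / (p1−p2)².

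For 40% versus 60%: p̄ = 0.50, z = 2.241 and 0.842, so n = [2.241·√0.50 + 0.842·√0.48]² / 0.04 = 117.5, that is 118 per group against 120 stated. (One-sided gives 97; two-sided with continuity correction gives 128.) At 120 versus 120 the power is 80.9%. For 40% versus 75% at 120 versus 80 it is 99.8%. The total is 120 + 120 + 80 = 320, so the stated size is right for two two-sided tests at 0.025.

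**2. Error for the two tests sized for.** The sum is 2 × 0.025 = 0.05. Both contrasts share the 120 not-frail patients, so their test statistics correlate at √(120/240 × 80/200) = √(0.5 × 0.4) = 0.447. Simulating two normal statistics with that correlation and rejecting if either exceeds 2.241 in absolute value gives 4.7%.

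**3. Error if both contrasts are also tested at 24 months at 0.025.** The upper bound is 4 × 0.025 = 0.10; under independence it is 1 − 0.975⁴ = 0.096. Both overstate it, because the tests share a reference group and the 24-month counts contain the 12-month events. The correlation between the 12- and 24-month statistics is not in the document and is assumed. Simulation with 1,000,000 draws gives:

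| Assumed 12/24-month correlation | P(at least one false positive) |
|---|---|
| 0.5 | 8.7% |
| 0.6 | 8.3% |
| 0.707 | 8.0% |
| 0.8 | 7.5% |

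A second simulation used chi-squared tests on binomial data with a constant annual risk of 20% or 40% (also assumed). It gives 8.2% and 8.5% for four tests, and 4.7% and 4.8% for the two 12-month tests.

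**4. Price of keeping both times primary.** Splitting 0.05 over four tests gives 0.0125 each, z = 2.498. Power for 40% versus 60% at 120 per group falls from 80.9% to 73.0%; 40% versus 75% keeps 99.5%. Restoring 80% needs 138 per group: 138 + 138 + 80 = 356 in total, or 320 × 138/120 = 368 if the 120:120:80 ratio is kept. No 24-month proportions are given, so power at 24 months cannot be computed.

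**The case against.** The strongest reply is that this is an observational cohort that will report rates with 95% confidence intervals, states no success rule, and may allocate error across time points in a statistical analysis plan that is not shown. The sample size is also arithmetically correct. All of that is fair, and a missing alpha allocation alone would not be a finding. What remains is that the protocol's own sections disagree on the primary time point, which a later plan could only resolve by overruling one of them. The protocol also sized the study on a controlled type-1 error and will report p-values.

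Several stronger readings are tempting and are not supported:

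- **The protocol plans four primary tests.** It never says so. Four comes from applying the two sized contrasts at both times named in the Statistical analysis section. The model might be tested once globally per time point, and other readings give two tests.
- **Error of 14–16%.** This needs every test read at 0.05, a level the protocol does not state.
- **An extra binary primary test.** No frail versus non-frail test of the event count is specified. The wording can be read as shorthand for each frail band against not frail; a two-group comparison is explicit only for mortality.
- **A competing survival analysis of events.** No survival model for cardiovascular events appears, so the label looks like an editing slip.
- **Conflicting frailty cut-points.** The labels under Frailty assessment are garbled, but no section gives different analysis bands.
- **Cardiovascular mortality as co-primary.** The Discussion lists among its primary questions whether frailty is "associated with the number of cardiovascular events and long-term cardiovascular mortality in a large, complete population with COPD", but the abstract and the outcome and analysis sections make mortality secondary. This is an editorial note.
- **The 12-month manuscript as a further test.** It is conditional on recruitment reaching the planned size, and its comparison is already among those counted.

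**Conclusion.** The point holds as a contradiction in the current text. The sample size section and the abstract's model sentence fix 1 year; the abstract's outcome sentence, the Aims, the Primary outcome and the Statistical analysis sections name 12 and 24 months. The 0.025 level is adequate for the two 1-year contrasts and for nothing more. The size of the problem is conditional: an excess of about 3 to 4 percentage points in family-wise error (7.5 − 4.7 = 2.8 to 8.7 − 4.7 = 4.0) if both contrasts are tested at both times at 0.025. It rests on that inferred set of tests and on the assumed correlation of 0.8 to 0.5. The contradiction itself needs no assumption. The time-to-event label, the two-group wording and the frailty labels are smaller inconsistencies in the same definition, to be corrected with it. The sample size is not in error.

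**What to change.** State one primary analysis: the number of cardiovascular events in the first 12 months, by zero-inflated Poisson regression, with CFS 4–5 versus 1–3 and CFS 6–8 versus 1–3, each at two-sided 0.025. This is the time point and pair of contrasts for which the level and the 320 patients were worked out, although more sections currently name both times. Then:

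- make the 24-month count a secondary outcome in the abstract, Aims, Primary outcome and Statistical analysis sections;
- delete the time-to-event label from the primary analysis sentence;
- reword the Primary outcome contrast to the three analysis groups, and align the labels under Frailty assessment with the bands in Power and sample size;
- as an editorial matter, bring the Discussion's description of the primary questions into line.

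These are wording changes and leave the sample size at 320. The cost is that the 24-month result carries no primary claim. If the sponsor wants both times primary, the protocol should say so, use 0.0125 per test, and state either the reduced power of 73% for 40% versus 60% at 120 per group or the larger sample of about 356 to 368.

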#### Inclusion criteria

Patients with age ≥40 years, with diagnosis of COPD of at least 1 year, in stable condition, without acute exacerbation in the last 30 days and/or all-cause hospitalisation in the last month, able to provide their written informed consent, will be included. Patients with concurrent diagnosis of asthma (asthma/COPD overlap syndrome) and alpha-1 antitrypsin deficiency are will also be included.

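### The primary model adjusts for age in three broad bands and leaves out smoking exposure and COPD severity, though both are collected, so it accepts avoidable residual confounding of the frailty effect

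*Protocol article*

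**What the plan says.** The Statistical analysis section compares the number of cardiovascular events between three frailty groups with a zero-inflated Poisson regression, "adjusting for sex, age (18–64, 65–80, >80) and frailty at the time of recruitment, and other clinically relevant non-respiratory comorbidities". The Inclusion criteria admit "Patients with age ≥40 years".

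The Baseline data section records smoking as "absence of smoking habit or active smoking expressed as pack/years", and also years of COPD, GOLD class 1 to 4, and GOLD grades under the 2011 and 2023 reports. None of these is in the primary adjustment set. GOLD enters the analysis only here: "Subgroups analyses (age, sex, GOLD classes and grades, comorbidities) will be conducted to assess the grade of frailty".

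The Introduction states: "Cardiovascular diseases share common risk factors with COPD such as ageing, active smoking, and sedentary lifestyle". It also says that people over 65 are more likely to live with frailty.

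**The concern.** In an observational cohort the adjusted estimate is the result. The protocol itself links age to frailty and to cardiovascular disease, so age is the clearest confounder. A banded covariate removes only the confounding between bands. The middle band spans 16 years of age and the lowest, in effect 40–64, spans 25. Frail patients will tend to sit at the older end of each, and that difference is credited to frailty.

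The second gap is that smoking exposure and COPD severity are measured but not used. Severity cannot be read into the comorbidity term, because that term is limited to non-respiratory conditions. The article states the list and the age cut-points outright, so an analysis plan that follows it would carry both weaknesses forward.

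**Working it through.** **1. The plan's own figure.** The article gives no figure for confounding. The nearest is the sample size, which shows whether the fix disturbs the design. For 40% vs 60%, two-sided α = 0.025 and power 80%:

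n = {z(1−α/2)·√[2p̄(1−p̄)] + z(power)·√[p₁(1−p₁)+p₂(1−p₂)]}² / (p₂−p₁)²
= (2.2414×0.7071 + 0.8416×0.6928)² / 0.04 = (1.585 + 0.583)² / 0.04 = 117.5, so 118 per group, against 120 stated.

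Power is 80.9% at 120:120 and 99.8% for 40% vs 75% at 120:80. The 320 reproduces. It rests on unadjusted chi-squared tests, so changing the covariates alters no stated figure.

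**2. Collected against used.**

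| Variable | Baseline data | Primary adjustment set |
|---|---|---|
| Age | yes | three bands |
| Sex | yes | yes |
| Comorbidities | yes | non-respiratory only |
| Pack-years | yes | no |
| GOLD class and grades | yes | no (subgroups only) |

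**3. What the age bands leave behind.** This is a large-sample Poisson simulation (without zero inflation) with a true frailty rate ratio of 1. All inputs are assumptions except the group split 120:120:80, which is from Power and sample size. Age has mean 70 and SD 9, truncated to 40–95. Each pair below is the fitted rate ratio for mild, then moderate/severe, against not frail.

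| Event rate ratio per 10 years | Frailty log-odds per 10 years | Unadjusted | Protocol bands | Continuous age |
|---|---|---|---|---|
| 1.3 | 0.5 | 1.078, 1.146 | 1.018, 1.029 | 1.001, 0.999 |
| 1.3 | 1.0 | 1.149, 1.296 | 1.043, 1.081 | 1.011, 1.020 |
| 1.5 | 0.5 | 1.110, 1.216 | 1.018, 1.036 | 0.994, 0.990 |
| 1.5 | 1.0 | 1.228, 1.476 | 1.053, 1.101 | 1.003, 1.007 |
| 2.0 | 0.5 | 1.209, 1.430 | 1.045, 1.082 | 1.004, 1.003 |
| 2.0 | 1.0 | 1.393, 1.906 | 1.076, 1.163 | 0.997, 1.004 |

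Per year of age, this grid covers event rates of +2.7% to +7.2% (1.3^0.1 = 1.027; 2.0^0.1 = 1.072) and frailty odds of +5.1% to +10.5% (e^0.05 = 1.051; e^0.10 = 1.105). Over the narrower range of +3% to +7% and +6% to +9%, the bands leave about 1.02–1.10 and continuous age about 0.99–1.00. In the least favourable corner of that range, the moderate/severe group taken alone reaches about 1.13.

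The bands do most of the work. In the last row, ln 1.163 / ln 1.906 = 0.151 / 0.645 = 23% of the log-scale age bias remains in the moderate/severe group.

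**4. An omitted binary factor.** Bias factor = [p₁(RR−1)+1] / [p₀(RR−1)+1], where p₁ and p₀ are its prevalence in frail and non-frail patients. This assumes the factor is independent of the covariates already in the model.

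- p₁ = 0.6, p₀ = 0.4, RR 1.5: 1.30/1.20 = 1.083
- the same prevalences, RR 2.0: 1.60/1.40 = 1.143
- prevalences reversed, RR 1.5: 1.20/1.30 = 0.923
- prevalences reversed, RR 2.0: 1.40/1.60 = 0.875

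The documents give neither the prevalences nor the effect, so neither the size nor the sign is fixed.

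**5. Scale against the design.** Converting the planning proportions to Poisson rates by −ln(1−p) gives 0.511, 0.916 and 1.386, so the planned rate ratios are 0.916/0.511 = 1.79 and 1.386/0.511 = 2.71. With 120:120 patients and an assumed 0.7 events each, SE(log RR) = √(2/84) = 0.154. A spurious ratio of 1.04 then raises the false-positive rate from 2.5% to about 3.0%, and 1.10 raises it to about 5.4%.

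**The case against.** The strongest reply is that the age bias is small beside the effects the study is built to find, and that every input behind it is assumed. Both points stand. A spurious 1.02–1.10 does not imitate a planned 1.79 or 2.71, and at the planned size it roughly doubles one test's false-positive rate at most over that range. But the bias is avoidable at almost no cost, and it weighs more if the true effect is smaller than planned.

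A reader might infer more than the documents support:

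- **That smoking biases the result towards the hypothesis.** The Introduction links smoking to COPD and cardiovascular disease, not to frailty. Patients with no smoking history are excluded, so only dose and current smoking vary, and nothing shows how these differ by frailty.
- **That site was collected and then ignored.** Site is not among the listed baseline variables. That it is known follows only from the multicentre design and the planned unit-level feedback. No text says that frailty scoring or event capture differs between countries.
- **That the 18–64 label or naming frailty among the adjusters distorts the estimate.** Nobody under 40 can enter, so the band operates as 40–64. Comparing three frailty groups needs a frailty term anyway. Both are matters of wording.
- **That the mortality models share the fault.** The article says only that they adjust for covariates, so the list is left to the analysis plan.

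GOLD class may also lie partly on the pathway between frailty and events. That is a reason to show both models, not to leave severity out without comment.

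**Conclusion.** The concern holds for the primary model. As written, it accepts residual confounding by age that continuous age would remove, and it sets aside two relevant baseline measures that the study already collects. The age part is modest: a spurious rate ratio of about 1.02–1.10 under the stated assumptions on age distribution, event gradient and frailty gradient, with none of these taken from the documents. The contribution of smoking or severity is possible but unquantified; the 8% to 14% in the working is an illustration and could take either sign. The documents do not support saying that a positive frailty finding would be an artefact.

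**What to change.** In the primary model:

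- enter age as a continuous term (linear plus a spline or quadratic term);
- add pack-years and GOLD class 1–4;
- report the frailty rate ratios with and without GOLD class;
- keep age bands for description only, relabelled 40–64, 65–80 and >80.

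A site or country term is a reasonable optional addition or sensitivity analysis. As an editorial change, name frailty as the exposure and not as an adjuster.

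The cost is a wording change with no new data and no change to the 320. Pack-years (1), GOLD class (3) and curvature in age (1–2) come to about 5–6 parameters without site, and linear age replaces the two band indicators. Confidence intervals will be slightly wider.
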